#### Primary Objectives 2-4: Immigrants Born in Poland or Ukraine

To maximize power among individuals born in Poland or Ukraine, we will include all eligible individuals and randomly assign them 1:1:1 to each of the 3 study arms. The number we will be able to include in the trial will most likely be higher in 2025 than in 2023 (Table 1) due to the age structure in these immigrant populations and due to new migration. Based on current national demographic statistics, we anticipate there will be some 6000 individuals aged 65 years or older from each immigrant group at the start of the trial. However, some 10% may be excluded due to not having a registered phone number, and a further 1% and 6% (Table 1) may be excluded due to influenza vaccination before the scheduled SMS dispatch date among the Ukrainian and Polish immigrant populations, respectively. Thus, we expect to be able to randomize 5346 Ukrainian immigrants, giving 1782 individuals in each study arm. With a baseline uptake rate of 3% (Table 1), a power of 0.8, and a 1-sided α of .05, this gives a minimal detectable coverage increase of 2 percentage points, adjusted for 3 pairwise comparisons. Similarly, we expect to be able to randomize 5076 Polish immigrants, giving 1692 individuals in each study arm. With a baseline uptake rate of 19% (Table 1), a power of 0.8, and a 1-sided α of .05, this gives a minimal detectable coverage increase of 4% points, adjusted for 3 pairwise comparisons.

In conclusion, the minimal detectable coverage increases of this trial fall within the range of effect sizes reported for other modes of nudging investigated in neighboring countries that share a similar influenza vaccination policy. Specifically, a recent study from Denmark reported that nudging by electronic letters increased coverage by approximately 1% points [26], while a recent study from Finland reported that nudging by ordinary mail on average increased coverage by approximately 6% points [25].

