### Assignment of Interventions

Assignment of treatment arm (control, intervention 1, and intervention 2) will be randomized, automated, and concealed. The identities of the participants will not be decipherable by the data managers.

We will use an external service provider to identify the eligible study population, perform the random selection and randomization procedures, and dispatch the SMS. The provider will be selected through a tendering process. All data management by the service provider will be done in close collaboration with and under the supervision of the project group. Data management, random selection, and randomization procedures will be performed with reproducible code that includes documented and adequate software functions, preferentially in R programming (R Foundation for Statistical Computing). For the Norwegian population, individuals in intervention arm 1 will be randomly selected from the whole eligible population, while the remainder of the eligible population will serve as the control arm. Similarly, we will use complete random assignment to treatment arm for the Polish and Ukrainian populations. Examples of R functions that serve these purposes are sample_n (from the *dplyr* package) and complete_ra (from the *randomizr* package). Random selection and randomization procedures will be performed after the assessment of the exclusion criteria. The project group will inspect the randomization code before dispatching the SMS.

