**National Population Register**		
	National ID	Used to identify eligible individuals and link to study ID. Not shared with InfluSMS project group
	Household composition	Variable identifying whether eligible individuals live in the same household, to enable sensitivity analyses
	Year of birth	Potential confounder (age)
	Sex	Potential confounder
	Vital status, with date	Exclusion of individuals who died or emigrated
	Country of birth	Determine if born in Poland or Ukraine
	Immigration date	Determine time living in Norway (potential confounder)

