### Statistical Methods

All individuals randomized will be analyzed, except individuals who die or emigrate during follow-up, who will be excluded from the analyses. We expect exclusions to be evenly distributed between treatment arms due to the randomized design. Additionally, we anticipate a low proportion of excluded individuals given the relatively short follow-up time of the trial. According to official statistics [33], we can expect approximately 2800 deaths and 100 emigrations per month among the nearly 1.1 million persons aged 65 years or older residing in Norway, which accounts for 0.3% of this population.

As recommended for binary RCT outcomes [34], coverage differences between treatment arms will be expressed on absolute and relative scales, that is, as percentage point differences and as relative risks, with associated 95% Wald CIs. The primary focus will be on absolute scale analyses because they may be most informative for public health decision-making. Absolute estimates will be derived from linear regressions [35], while relative estimates will be derived from generalized linear models with a log-binomial link function [36]. Overall interactions (specifically secondary objectives 1 and 2, where differences between treatment arms will be compared between country backgrounds) will be assessed by likelihood ratio tests and, if significant, further analyzed by the participation differences between factor levels of the variables that interact.

We will compare the time to vaccination (ie, the number of days elapsed between the SMS dispatch date and the influenza vaccination date) between trial arms by the Kaplan-Meier method and the log-rank test.

We assume the registry data for randomized individuals to be close to complete and thus will not impute missing values.

As sensitivity analyses, we will exclude households consisting of at least two or more people aged 65 or older. Comparing the results of these analyses with the main results will indicate whether there may be spillover effects of the SMS interventions within households. Moreover, it will exclude persons living in nursing homes, who may experience easier access and less autonomy regarding influenza vaccination. In exploratory analyses, we will also address the potential effects of SMS nudging for influenza vaccination on the coverage of COVID-19 vaccination. We will use the same statistical methods for these sensitivity and exploratory analyses as described for the main analyses.

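### Dropping households with two or more older adults cannot isolate within-household spillover; a contrast by the co-resident's assignment, from data already collected, would address it directly

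*Protocol article*

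**What the plan says.** The protocol article, Statistical Methods, describes the restriction as follows: "As sensitivity analyses, we will exclude households consisting of at least two or more people aged 65 or older". It then says what the comparison is for: "Comparing the results of these analyses with the main results will indicate whether there may be spillover effects of the SMS interventions within households". The next sentence gives the same restriction a second purpose: "Moreover, it will exclude persons living in nursing homes, who may experience easier access and less autonomy regarding influenza vaccination". The sensitivity analyses use the same methods as the main analyses, so they remain comparisons between arms, with the absolute difference as the primary focus and relative risks alongside.

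Allocation is by individual. In Assignment of Interventions, the general-population rule reads: "individuals in intervention arm 1 will be randomly selected from the whole eligible population, while the remainder of the eligible population will serve as the" (the sentence closes by naming the comparison group). For the immigrant groups: "we will use complete random assignment to treatment arm for the Polish and Ukrainian populations", and the Sample Size section adds "we will include all eligible individuals and randomly assign them 1:1:1 to each of the 3 study arms". No household clustering or stratification is mentioned.

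The data for a different analysis are already planned. Data Collection puts the household ID, treatment arm and exclusion status of everyone born in 1960 or earlier in the key file. Table 3 lists a "Variable identifying whether eligible individuals live in the same household, to enable sensitivity analyses". Under Stratified Analyses, strata by household composition are planned as well.

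**The concern.** Because people are randomised one by one, a participant's own arm says almost nothing about whether a co-resident got an SMS. Control and SMS arms are equally exposed to co-residents' messages, so removing shared households need not change the arm difference even if spillover is large. Agreement between the two results could be taken as reassurance that it does not give. A disagreement could be put down to spillover when it reflects a different response among older adults who have no older co-resident.

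At stake is how the result carries over to a programme. The cost-utility model is to be built on coverage differences observed in the trial, and the Discussion looks to nationwide use, where both members of a couple would be messaged. Additive spillover would be absent from the trial difference but present at roll-out. Saturating spillover would dilute the trial difference in shared households.

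**Working it through.** **The plan's own figures.** The article gives no number for spillover. Its arm sizes, used as inputs, are 23,485 × 0.80 = 18,788 (general population, SMS arm), 5346/3 = 1782 (Ukraine) and 5076/3 = 1692 (Poland). Baseline uptake *b* is 60%, 3% and 19%; the detectable increases, used as the direct effect *d*, are 1, 2 and 4 points.

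**Probability *p* that a co-resident gets an SMS.** General population: 1.1 million × 0.80 = 880,000, and 18,788/880,000 = 2.1%; controls number 880,000 − 18,788 = 861,212. Immigrant groups, 1:1:1: *p* = 2/3, if the co-resident belongs to the same trial population.

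**Assumption.** The share *h* living with one other randomised older adult is not in the documents; 0.3, 0.5 and 0.6 are used.

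**Step 1, additive spillover of *s* points.** Arm difference in pairs = (*b* + *d* + *ps*) − (*b* + *ps*) = *d*, whatever *s* is. In 200 simulated general-population trials with *d* = 1, *s* = 5 and *h* = 0.5, the main and restricted estimates were both 0.986, difference 0.00 (SD 0.36).

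**Step 2, saturating spillover (one SMS serves both).** Arm difference in pairs = *d* − *ps*, so restricted minus main = *hps*. The samples are nested, so the SE of that shift is √(V/(1−*h*) − V), with V = *b*(1−*b*)(1/n₁ + 1/n₀). Power is for a one-sided .05 test, with *s* = *d*. The last column gives the shift with no spillover at all but a direct effect half as large in shared households, which is *hd*/2.

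| Population | Shift, saturating (points) | SE (points) | Power | Shift, no spillover, halved effect (points) |
|---|---|---|---|---|
| General, *d* = 1 | 0.006–0.013 | 0.24–0.44 | about 5% | 0.15–0.30 |
| Poland, *d* = 4 | 0.8–1.6 | 0.88–1.65 | 23–26% | 0.6–1.2 |
| Ukraine, *d* = 2 | 0.4–0.8 | 0.37–0.70 | 28–32% | 0.3–0.6 |

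In the general population the limit is *p*, not the model. Even if the own-SMS effect were 5 points smaller when the co-resident was also messaged, the shift at *h* = 0.6 would be 0.6 × 0.02135 × 5 = 0.06 points, against an SE of 0.44.

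**Step 3, relative scale.** Additive spillover does not cancel in the relative risk. Ukraine with *b* = 3, *d* = 2, *s* = 2: 5/3 = 1.67 without an older co-resident, and (5 + 1.33)/(3 + 1.33) = 6.33/4.33 = 1.46 in pairs.

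**Step 4, a direct contrast.** Compare controls whose co-resident was randomised to SMS with controls whose co-resident was randomised to control. Group sizes are *h* × n₀ × *p* and *h* × n₀ × (1−*p*). Detectable spillover is (1.645 + 0.842) × SE, for 80% power at one-sided .05.

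| Population | Exposed controls | Unexposed controls | SE (points) | Detectable (points) |
|---|---|---|---|---|
| General | 5,516–11,032 | 252,848–505,695 | 0.67–0.47 | 1.7–1.2 |
| Poland | 338–677 | 169–338 | 3.7–2.6 | 9.2–6.5 |
| Ukraine | 356–713 | 178–356 | 1.6–1.1 | 3.9–2.8 |

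In the Step 1 simulation this contrast returned 5.00 points for a true 5.

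**Step 5, household size.** The contrast is randomised only for a fixed number of randomised members. With *p* = 2.1%, the chance of at least one messaged co-resident is 2% in a pair. In homes of 10, 20 or 40 randomised residents (assumed sizes) it is 1 − (1−*p*)⁹ = 18%, 1 − (1−*p*)¹⁹ = 34% and 1 − (1−*p*)³⁹ = 57%. Pooling all households of two or more would load the exposed group with nursing-home residents.

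**The case against.** A reader might infer that the planned comparison can show nothing about spillover. The documents do not support that. With 1:1:1 allocation in the immigrant groups, independent assignment is exactly what would contaminate controls if one message serves a household: with *d* = *s* = 2 points, the difference among pairs falls to 2 − (2/3 × 2) = 0.67. Dropping shared households responds to that, though with low power. The relative risks, also planned, can move even under additive spillover (Step 3). Both points stand and limit the criticism to isolating spillover.

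The wording is also cautious: it speaks of indicating a possibility, not of estimating an effect. The restriction has a legitimate second purpose in nursing homes, effect modification is already covered by the household-composition strata, and an article may leave a further contrast to the full plan. These points reduce the weight of the concern. They do not rescue the stated inference, because in the largest population the comparison carries practically no information on spillover, and in the other two a shift of the size saturation would produce also arises with no spillover.

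Nor should a reader infer that the primary analysis is invalid. It remains a comparison of arms as randomised.

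**Conclusion.** The concern holds in limited form: the comparison cannot isolate within-household spillover. On the absolute scale it is blind to additive spillover. In the general population it is practically uninformative under any of the models considered, because only about 2% of co-residents are messaged. In the Polish and Ukrainian groups saturation could move it by up to about 1.6 and 0.8 points, with power of 23 to 32%, and the shift would be mixed with household type and the removal of nursing-home residents.

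The sizes rest on assumed co-residence of 30 to 60%, two-person households, and immigrant co-residents drawn from the same trial population; with a general-population co-resident, *p* there is about 2% instead of two thirds. The algebraic cancellation needs only individual randomisation. This concerns a sensitivity analysis and its interpretation; the primary estimate, test and sample size are unaffected.

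**What to change.** 1. Keep the restriction, described as a sensitivity analysis for household type and nursing-home residence alongside the household-composition strata. Replace the spillover sentence, and state that agreement with the main result is not evidence of no spillover.
2. Add a contrast using the household ID and arm in the key file. In households with exactly two randomised members (or conditioning on the number of randomised members), with institutions excluded, compare control-arm members whose co-resident was randomised to SMS with those whose co-resident was randomised to control. Take account of the trial population to which the co-resident belongs.
3. Present it as the main spillover analysis in the general population and as exploratory in the Polish and Ukrainian groups, where it is imprecise.
4. Reconcile Sample Size, which has early-vaccinated people excluded after randomisation, with Assignment of Interventions, which randomises after exclusions are assessed. This decides who counts as a randomised co-resident.

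The cost is one reworded sentence and one added analysis of data already to be collected.

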### Data Monitoring

The trial does not pose any harm to participants; thus, the project does not have a data monitoring committee or plans for auditing of trial conduct. Similarly, there will be no interim analyses before the end date of follow-up and no stopping guidelines for the trial.

### Ethical Considerations

We have submitted the project for initial evaluation to the Regional Committees for Medical and Health Research Ethics, who recently determined that the project does not fall under the jurisdiction of the Health Research Act [40] (reference #787321). We will thus apply for exemption from the duty of confidentiality from the Health Directorate. The rationale for this decision was that the objective of the research is not to gain new knowledge on health and disease as such, with reference to paragraphs 2 and 4a of the Health Research Act. The application was considered by the REK sør-øst B committee.

This study cannot be performed based on informed consent. Exemption from the duty of confidentiality gives a permit to access and merge the personal registry data without obtaining informed consent. We have conducted several similar registry-based studies. It is our experience that exemption for the duty of confidentiality is granted for studies of this nature, that have large potential public health benefits and no direct consequence for participants [41-44]. The registries own their data and will grant the project data access based on the permits we supply in our data application (ie, exemption from the duty of confidentiality).

Smartphone numbers will be accessed through the Contact and Reservation Register, in which every Norwegian citizen who has logged into a Norwegian public service using an electronic ID is registered. Individuals can opt out of the register, and those who have done so will not receive an SMS as part of this study. About 95% of the adult Norwegian population is part of the Contact and Reservation Register. Opting out will not be considered in the analyses in this pragmatic trial because access to smartphone numbers would be through the same register if SMS reminders were part of the influenza vaccination program. We expect that the drop-out rate will be similar across treatment arms due to the randomized design.

We will submit the protocol and approvals together with a dedicated data protection impact assessment for assessment by the data protection officer at the National Institute of Public Health. The data protection officer oversees data processing in research projects to ensure it is in accordance with applicable data protection laws. The main principles regarding data protection and confidentiality in the project are described in the Data Collection and Data Management sections.

In case of protocol amendments, all stakeholders that have granted approvals to the project, as well as Clinicaltrials.gov, will be notified. None of the project members have any financial or other conflicting interests to declare.

Data access is contingent on the specific permits described above. Thus, data are only accessible to project members. To advise the project, users of Polish, Ukrainian, and Norwegian origin will be part of the project group. We will also have focus groups with users from each nationality to help formulate acceptable and adequate SMS nudges.

### Dissemination

We plan to publish the protocol and the findings of the trial in international peer-reviewed scientific journals. Authorship will be granted according to the Vancouver Convention. Professional writers will not be used.

The findings will also be presented at national and international conferences. To inform the public, we will publish information about the trial on a project web page. Information aimed at the public will mainly be in Norwegian. Further, we will present the project to various stakeholder groups, notably the main user groups of the study (organizations for older adults and immigrant groups) and public health organizations.

## Results

As of July 3, 2024, the project has received funding for protocol development from Foundation Dam (grant SDAM_FOR-558766) and we are in the process of obtaining permits, agreements, and access to the infrastructure needed to conduct the trial. Inclusion of participants will start in the third quarter of 2025 and the outcome registry data will be available in the first quarter of 2026. We plan to publish the results during the fourth quarter of 2026.

The results will be reported according to the Consolidated Standards of Reporting Trials (CONSORT) statement on eHealth [45,46]. We will present the baseline characteristics of the 3 study populations, and describe the coverage by treatment arm and population, for strata of age, sex, and duration of residency. We will present the absolute and relative coverage differences between the treatment arms as described in objectives 1-4. In addition, we present comparisons of effect sizes between populations as described in secondary objectives 1 and 2, on absolute and relative scales. The primary focus will be on absolute scale analyses for the coverage analyses (primary outcome measure). We also compare the time to vaccination between treatment arms (the secondary outcome measure). All effects are presented with 95% CIs. We also present the likelihood ratio test *P* value for interaction terms. Table shells for the analyses described earlier can be found in Multimedia Appendix 1. The main findings may also be illustrated in the figures.

## Discussion

This pragmatic RCT will provide insights into the effectiveness of SMS reminders in improving influenza vaccination coverage among older adults, which was specifically mentioned as a knowledge gap in a recent review on this topic [23]. The trial will estimate the effectiveness in the older adult population in Norway at large, and among older adult immigrants from Poland or Ukraine, which are large immigrant populations that have a particularly low influenza vaccination coverage in Norway. For the immigrant populations, the trial will also address whether the language of their adopted country may represent a barrier to influenza vaccination uptake that can be reduced by SMS nudging in the official language of their native country. If SMS nudging is effective, it is a strategy that may be feasible for implementation in a nationwide influenza vaccination program because it is scalable, inexpensive, and non-intrusive. Since influenza vaccination protects against influenza and its sequelae, a higher influenza vaccination coverage will benefit society through lower health care costs, as well as the individuals who get vaccinated through direct protection against influenza.

Strengths of this trial include the use of data on nearly all individuals aged 65 years or older residing in Norway, whose health and administrative data are captured in nationwide registries without any loss to follow-up. This eliminates selection and response biases associated with surveys, ensures high quality of the main outcome measure of the trial, that is, influenza vaccination coverage, and yields results that are valid at the national level. Further characteristics that contribute to the high internal validity of this study include the randomized design, no experimenter bias, and standardized procedures for all participants. This trial also has high external validity since it is conducted in real life and will thus yield data that will be entirely representative of how these interventions would work should they become part of an adult vaccination program. Moreover, the results are likely to be of relevance internationally, both as a proof of concept of whether SMS interventions might be effective in increasing adult vaccination coverage and more directly for the immigrant groups addressed here, which likely experience similarly low coverage, for similar reasons, in other adopted countries. The trial will also establish the feasibility of implementing an SMS nudging intervention using the infrastructure available in Norway, for instance in terms of timely access to the necessary health and administrative registry data. Novelty is another strength of the study since we are not aware of other trials with similar interventions and objectives. The trial will also be informed by users, which may enhance its relevance to the populations targeted by the interventions.

The trial also has several limitations, most of which relate to the number of Polish and Ukrainian immigrants we will be able to randomize. First, the number of persons in the immigrant groups who are aged 65 years or older in the 2025-2026 influenza season is a moving target that will be influenced by the influx and outflux of people by that time, as well as the exact underlying age distribution of these immigrant populations. Second, our estimates of the fraction of people missing a registered smartphone number are based on statistics for the whole Norwegian population, and we do not know whether this fraction may be different for the Polish and Ukrainian sub-populations. Third, the minimum detectable effect size for the Polish and Ukrainian populations is approximately 4% and 2% points, respectively. This may be a limitation because even smaller effect sizes might be of public health interest for an inexpensive intervention. Finally, even though we will initiate the trial at the very start of the influenza season, some people will already have been vaccinated by this point, and they will be excluded from participation in the trial. The number of excluded individuals will depend on national vaccine distribution logistics and the epidemiology of influenza in the trial season, which are beyond our control.

The current influenza vaccination program lacks an individual cue to action, which could potentially be more effective than a general recommendation that lacks personalization or direct communication. Sending SMS nudges for influenza vaccination is one way to make individual contact that is likely to reach a very large proportion of the eligible population. If sending SMS reminders is effective, even small effect sizes may benefit public health and be cost-effective. Furthermore, nudges tailored to immigrant groups that have very low uptake of influenza vaccine may reduce inequalities in the use of this preventive health care service and, thus, in health. Insights from the interventions investigated in the current trial can extend to other vaccination contexts and be of international relevance.

